##### Secondary outcomes

The secondary endpoints for the trial includes continuous, categorical and time-to-event data items. Any secondary endpoints that are continuous in nature will be analysed in the same way as described for the primary outcome. For dichotomous secondary endpoints, the proportion of participants and percentages will be compared between arms using a log-binomial model. Relative risks and 95% CIs will be calculated. For any time-to-event outcomes these will be compared between treatment arms by using survival analysis methods. Cox proportional hazards model will be used and treatment effects will be expressed as HRs with 95% CIs. Kaplan-Meier survival curves will be constructed for visual presentation of time-to-event comparisons.

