### Outcome measures

The primary outcome is TTR at 12 months. Secondary outcomes include (1) TTR at 6 months; (2) thromboembolic and bleeding events from at 12 months; (3) composite MACE outcome of non-fatal MI, non-fatal stroke and cardiovascular death and all-cause mortality, in an exploratory analysis (combined and individually) at 12 months; (4) change in patients’ knowledge of AF from baseline to 6 months and 12 months; (5) cost effectiveness; (6) quality of life at baseline, 6 months and 12 months assessed using the 5-level EQ-5D version (EQ-5D-5L) (Thai version)^29 30^ and (7) patient satisfaction/perceptions of the TREAT intervention. An embedded qualitative study will assess patient perceptions of the TREAT intervention.

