### Statistical analysis

Continuous variables will be presented as mean (SD), or median (IQR), as appropriate; categorical variables will be reported as counts with percentages. Descriptive statistics will be presented for baseline demographic and clinical information. For all major outcomes, summary statistics and differences between groups (eg, mean differences and relative risks) will be presented, with CIs and p values from two-sided tests also given.

All analyses will be based on the intention-to-treat (ITT) principle. The primary comparison groups will be composed of those randomised to Group 1, usual care, versus those randomised to Group 2, the SAMe-TT_2_R_2_ score-guided strategy with the TREAT intervention (plus usual care). All outcomes will be adjusted for the stratification variables (centre, sex and baseline SAMe-TT_2_R_2_ score) where possible. Two-tailed p values <0.05 will be considered statistically significant. No adjustment for multiple comparisons will be made.

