#### Analysis of outcome measures

##### Primary outcome

The primary outcome is the TTR at 12 months and differences in TTR between the intervention and usual care groups will be examined using a linear regression model. Results will be presented as mean difference and 95% CI. A key assumption for this analysis is that the data will be normally distributed; this assumption will be examined visually based on the residuals from the fitted model. If data are deemed not to be normally distributed, then the Mann-Whitney U test will be used for analysis.

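### The continuous secondary analyses name no baseline-outcome covariate for knowledge and EQ-5D-5L, which costs precision and leaves these comparisons open to chance baseline imbalance

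*Protocol article*

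**What the plan says.** All references are to the protocol article.

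- **Primary outcome:** "differences in TTR between the intervention and usual care groups will be examined using a linear regression model". If residuals look non-normal, the plan changes method: "If data are deemed not to be normally distributed, then the Mann-Whitney U test will be used for analysis".
- **Statistical analysis:** "All outcomes will be adjusted for the stratification variables (centre, sex and baseline SAMe-TT_2_R_2_ score) where possible".
- **Secondary outcomes:** "Any secondary endpoints that are continuous in nature will be analysed in the same way as described for the primary outcome".
- **Outcome measures** lists two continuous endpoints with a baseline measurement. One is "change in patients’ knowledge of AF from baseline to 6 months and 12 months". The other is "quality of life at baseline, 6 months and 12 months assessed using the 5-level EQ-5D version", which gives measurement times but does not say whether the arms are compared on follow-up scores or on change.
- **Table 2** schedules the questionnaires at baseline, month 6 and month 12, and the TREAT intervention at month 1. The baseline scores therefore precede the intervention.
- **Health economics, Data analysis** plans adjustment for baseline covariates, which it does not name, in the cost-per-QALY analysis.

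**The concern.** A model for TTR needs no baseline-outcome term, because anticoagulant-naïve patients have no earlier TTR. Knowledge and EQ-5D-5L differ: each patient's own earlier score is likely to be the strongest available predictor of the later one. Carrying the TTR model over to them names no such term.

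Two things follow. First, precision is lost. Second, a chance difference between the arms at baseline passes into the estimate. With a follow-up score, an arm that starts higher looks better. With a change score, regression to the mean makes it look worse.

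Knowledge is a direct target of an educational intervention, and EQ-5D-5L carries the quality-of-life result. The trial is sized for TTR alone, so avoidable noise in these two endpoints is not covered by any power statement.

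**Working it through.** **The plan's own figure.** The inputs in Sample size and power calculations are a difference of 10, SD 26, two-sided 5% and 90% power.

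- Normal approximation: 2 × (1.960 + 1.282)² × 26² / 10² ≈ 142.1, so 143 per arm.
- The t-test solution is 143.03, so 144 per arm and 288 in total.
- Attrition: 288 / 0.9 = 320.

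The stated sample size reproduces, and this point does not touch it.

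**Inputs for the comparison.** I take 144 evaluable per arm from the same section. The correlation r between baseline and follow-up score is not in the documents, so it is assumed over 0.3 to 0.7. The variance is assumed equal at both times, and r is the correlation left after centre, sex and score.

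**Formulas.** The variance of the arm difference, in units of 2σ²/n, is:

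- follow-up score: 1
- change score: 2(1 − r)
- ANCOVA: 1 − r²

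The standard error (SE) in SD units is √(2 × factor / 144).

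| r | Factor: change | Factor: follow-up | Factor: ANCOVA | SE: change | SE: follow-up | SE: ANCOVA |
|---|---|---|---|---|---|---|
| 0.3 | 1.40 | 1 | 0.91 | 0.139 | 0.118 | 0.112 |
| 0.5 | 1.00 | 1 | 0.75 | 0.118 | 0.118 | 0.102 |
| 0.7 | 0.60 | 1 | 0.51 | 0.091 | 0.118 | 0.084 |

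**Variance reduction with ANCOVA**

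- Against change (knowledge): 1 − 0.91/1.40 = 35%; 1 − 0.75/1.00 = 25%; 1 − 0.51/0.60 = 15%.
- Against follow-up (EQ-5D-5L, if compared that way): 1 − 0.91 = 9%; 1 − 0.75 = 25%; 1 − 0.51 = 49%.

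**In terms of power.** Take an effect that ANCOVA detects with 80% power, d = (1.960 + 0.842) × SE(ANCOVA). Power under another estimator is Φ(d/SE − 1.960). At r = 0.5, d = 2.802 × 0.102 = 0.286 SD and power is Φ(0.286/0.118 − 1.960) ≈ 68%. Over r = 0.3 / 0.5 / 0.7:

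- change score: 62% / 68% / 73%
- follow-up score: 76% / 68% / 52%

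**Chance imbalance.** The SE of the baseline difference is √(2/144) = 0.118 SD. A difference above 0.2 SD in either direction has probability 2 × (1 − Φ(0.2/0.118)) ≈ 9%, if baseline is unrelated to the strata. Given a difference of 0.2 SD:

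- the follow-up estimate shifts by 0.2r = +0.06 / +0.10 / +0.14 SD
- the change estimate shifts by −0.2(1 − r) = −0.14 / −0.10 / −0.06 SD
- the ANCOVA estimate shifts by about 0

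A simulation of 10,000 trials at each r agreed with these standard errors and shifts. It showed all three estimators centred on the true difference.

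**The case against.** The strongest reply is that a condensed article is being read as a closed model. The sentence on stratification variables sets a minimum and forbids nothing further. The Secondary outcomes sentence is generic, and an analysis plan that is not shown may name the baseline score. That reply stands against any claim that the plan adjusts *only* for centre, sex and score; a reader might infer this, but the text does not say it. It does not remove the point. The article does fix a rule for these endpoints, and the rule is borrowed from an outcome with no baseline.

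Three other inferences should be resisted.

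- **That baseline knowledge is ignored.** It enters by subtraction, and a change score is a legitimate estimator. The point about knowledge is efficiency and regression to the mean.
- **That the results would be biased.** Over randomisations all three estimators are unbiased. The shifts above are conditional on an imbalance that arose by chance.
- **That the loss is large.** It depends on r, which is unknown. For EQ-5D-5L at r = 0.3 it is only 9%, and the follow-up comparison is itself an assumption.

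It can also be said that baseline adjustment is already planned for EQ-5D-based results. The stated adjustment belongs to the cost-per-QALY analysis and does not cover the quality-of-life comparison listed as a secondary outcome. It does show that the investigators accept the principle.

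**Conclusion.** The point holds as a matter of precision and of sensitivity to chance imbalance in two secondary endpoints. As written, knowledge and EQ-5D-5L take a model that names no baseline-outcome term, although the baseline values are collected. Over assumed correlations of 0.3 to 0.7, the avoidable variance is 35% down to 15% for knowledge as a change score, and 9% up to 49% for EQ-5D-5L as a follow-up score. These figures rest on equal variances at both times, 144 evaluable per arm, and the assumed r. The TTR analysis and the sample size are not affected.

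**What to change.** Add one sentence to the secondary analysis: AF knowledge and EQ-5D-5L at 6 and 12 months are each modelled on treatment arm with the baseline value of the same measure as a covariate, in addition to centre, sex and SAMe-TT2R2 score, and the adjusted mean difference with its 95% CI is reported at each time. A repeated-measures model with baseline as a covariate would serve equally well.

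The same sentence should say that the adjusted estimate is reported even if residuals look non-normal, because the Mann-Whitney fallback takes no covariates and would drop the baseline term again.

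The cost is one sentence in the analysis plan. It needs no new data, visits or patients.

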### Qualitative study

Qualitative data will be obtained directly from patient interviews and interviews with healthcare professionals delivering the intervention as part of an embedded qualitative substudy. A purposive sample of 10–15 participants from the intervention arm will take part in one-to-one semi-structured interviews with a qualitative researcher, at two time-points (within 4 weeks of the intervention and at 6-months follow-up). Interviews will explore participants’ experience of AF; of receiving the TREAT intervention; their perspectives on the utility of different interventions components; as well as behavioural modifications resulting from the intervention. Staff delivering the intervention at each study site will also be interviewed to understand their perceptions of the TREAT intervention and their experience of delivering it to patients. A thematic analysis of interview content will be informed by the framework analytic approach. Audio-recorded interviews will be translated and transcribed into English in order to facilitate team-based analysis by Thai and English research team members.^31^

### Health economics analysis

The economic evaluation will determine the cost effectiveness of the intensive educational intervention versus usual care. The evaluation will take the form of an incremental cost–utility analysis to estimate cost per quality adjusted life year (QALY) over 12-months follow-up from a Thailand health service perspective. If differences in TTR are achieved in the trial, a longer-term Markov model-based cost per QALY analysis will be also undertaken.

#### Data collection

Data will be collected on healthcare utilisation required for the intervention, warfarin therapy and monitoring, and healthcare visits, hospitalisations, investigations and medication related to thromboembolism, bleeding and management of AF. Information will be collected at the 6-month and 12-month patient visits from trial CRFs and hospital records. Additional costings, such as those associated with transportation to the hospital, will be collected from the patients. The EQ-5D-5L (Thai version) questionnaire will be administered to participants at baseline, 6 months and 12 months to estimate QALYs.

#### Data analysis

Unit costs from standard Thai sources will be applied to all healthcare resource use items, and mean resource use (for each category of healthcare usage) and mean total costs will be calculated for both trial arms. The current Thailand’s value set will be applied to patient EQ-5D-5L responses to obtain utility scores and QALYs will be calculated using the area under the curve approach. Multiple imputation will be used to impute all missing values for the EQ-5D-5L and total cost estimates for non-responders. As cost and QALY data are likely to have a skewed distribution, a non-parametric comparison of means (using bootstrapping) will be undertaken. A cost–consequence analysis will initially be reported, describing all the important results relating to resource use, costs and consequences. Incremental cost-effectiveness and cost–utility analyses will then be undertaken to estimate the incremental cost per QALY gained at 12 months, with adjustment for baseline covariates. The robustness of the results will be explored using sensitivity analysis. Cost-effectiveness acceptability curves (CEACs) will also be produced to reflect the probability that the intervention will be cost effective at different cost per QALY willingness to pay thresholds.

#### Model-based analysis

If the trial data show a benefit in TTR due to the intervention, trial results will be extrapolated using a Markov model-based cost per QALY. This model will take into account the long-term impact of anticoagulant control on thromboembolism and bleeding over the patient’s lifetime, with costs and outcomes discounted at 3%. The model structure will be informed by previously published modelling studies and expert opinion. Extensive deterministic sensitivity analysis using predefined ranges will be undertaken to explore which model parameters have most impact on cost effectiveness. Parameter estimates will be incorporated into the model as distributions to allow for a probabilistic sensitivity analysis, with CEACs constructed to assess the probability of cost effectiveness at different cost per QALY willingness to pay thresholds.

### Trial status

The study protocol V.2.1 dated 19 August 2019 was approved by the Institutional Ethical Committee of each study site and by the IRB of the Ministry of Public Health, the Royal Government of Thailand (CREC number: COA-CREC 007/2020) and the study protocol had amended and approved at V.3.0 dated 9 June 2020. The recruitment of participants started in 31 January 2020. Last patient recruitment is expected in May 2021. Data collection is expected to be completed in December 2021.

### Dissemination

Results of this trial will be submitted for publication in a peer-reviewed journal. The manuscript will be prepared by the principal investigators or their delegates and authorship will be determined by the trial publication policy. Participants will be informed of the outcome of the trial via a link to a preview of the publication. A lay summary will also be provided via email or posted to participants prior to publication.

## Data Availability

Data are available upon reasonable request.
